#### Flow of participants

The flow and number of participants through assessment of eligibility, randomization, follow-up, and analysis will be presented (Fig. 2) along with reasons for exclusions and withdrawals for all time points.

**Fig. 2 Fig2:**
[figure not shown]
Trial profile

#### Comparability between the two groups

Summary values (means, proportions) for sociodemographic characteristics among the groups will be presented in the baseline table. We will not perform any test of significance. Our large sample size is likely to yield a balance between the groups. However, we will carefully examine the size of any baseline differences. Imbalanced characteristics that may influence the primary outcomes will be adjusted appropriately.

#### Main effects

Analysis will be done by intention-to-treat. Mean (SD) birth weight, birth length, LAZ score at 24 months, proportion of preterm birth and spontaneous preterm birth, SGA, LBW, stunting at birth and 24 months will be presented for the different groups.

For binary outcomes, generalized linear models (GLMs) of the binomial family with a log-link function will be used to calculate the effect size [relative risk and 95% confidence interval (CI)]. For continuous outcomes, GLMs of the Gaussian family with an identity-link function will be used to calculate the effect size (difference in means and 95% CIs). The effect of interventions on secondary outcomes will be assessed using the same models as for primary outcomes.

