We propose to enrol a total of 13,500 eligible women (6750 in pre- and peri-conception intervention package group and 6750 in control group) based on the following assumptions: 45% of reproductive-age women randomized get pregnant in the 18 months of the pre- and peri-conception intervention period, 30% loss (abortions, still births, maternal deaths, moving away, refusals) between pregnancy and live birth and 20% loss (loss-to-follow-up and child deaths) between birth and 24 months of age.

We will get ~ 1100 live births per group. This will enable us to detect a 25% difference in preterm births, proportion LBW and SGA between pre- and peri-conception package alone and control group (A + B vs C + D) and enhanced antenatal, postnatal and early childhood care alone and control group (A + C vs B + D) and a mean difference of 0.15 SD in LAZ score at 24 months for the above comparisons.

We will get at least 600 children in each of the four groups (A, B, C, D) at 24 months. We will be able to detect 0.2 SD difference in mean LAZ score at 24 months and 0.2 SD difference in birth weight and birth length between pre- and peri-conception intervention package and enhanced antenatal, postnatal and early childhood care and control group.

The sample size of ~ 2400 (at least 600 children in each of the 4 groups) at 24 months of age will also allow us to detect an interaction odds ratio (lOR) of ≥1.70 to 1.85 in the proportion of stunted children among short mothers (< 150 cm) and among tall mothers (≥ 150 cm) between the control (routine care) and the intervention group who received the intervention package throughout, with 80% power and 95% confidence level.

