### Intervention delivery

#### Pre- and peri-conception period

The intervention delivery team conducts the first visit post enrolment and three-monthly follow up visits thereafter for a period of 18 m or till the women gets pregnant. At the first visit, symptoms of RTI and tuberculosis (TB) are ascertained and a history of epilepsy is taken. Blood pressure is measured (Omron 1300 digital blood pressure device) [59]. A blood specimen taken to check for anemia (hemoglobin - Hb), diabetes (Glycated hemoglobin - HbA1c), thyroid disorder (Thyroid-stimulating hormones - TSH) and syphilis (Rapid plasma regain; RPR).

Women with severe anemia (Hb < 8 g/dl), prediabetes (HbA1c 5.7% to 6.4%), diabetes (HbA1c ≥6.5%), high blood pressure (≥140/90 mmHg; at least two measurements 48 h apart), hypo- (TSH > 5.5 IU/mL) or hyper-thyroidism (TSH < 0.4 IU/mL), presence of symptoms of suspected TB, RPR positivity, reporting of symptoms of RTI or sexually transmitted diseases (STI), epilepsy and severe undernutrition (BMI < 16 kg/m^2^) are referred to the collaborating tertiary care hospital (Safdarjung Hospital). An outreach clinic manned by study physicians, nutritionists, psychologists and laboratory staff has been set up in the study area. Women with mild to moderate anemia (Hb 8 to < 12 g/dL) are treated with iron-folic acid for three months or till they are non-anemic. Women with RTI or STI are managed in the outreach clinic or hospital using algorithms of the syndromic approach [60]. Family planning advice is offered to recently (< 1 year) married women, those with a young (< 1 year) child and if women have moderate to severe anemia, symptoms and signs of RTI/STI, undernutrition, hypo- or hyper-thyroidism and diabetes requiring treatment.

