#### Pregnancy, postnatal and early childhood period after the second randomization

When a pregnancy is reported, trans-abdominal ultrasound (GE ultrasound Voluson S8, PI Healthcare Inc., [name]) is done between 9 and 13 weeks of gestation. If women are eligible at rescreening (not moving away from the study area) and consent is given for further participation in the study, they are randomized to either receive Enhanced Antenatal, Postnatal and Early Childhood Care (national and/or WHO-recommended interventions delivered well - intervention group) or routine care (control group). Each woman is allocated to a worker in the intervention delivery team for pregnancy. This worker visits the women monthly and ensures registration in Safdarjung Hospital (if the woman does not want to go to Safdarjung Hospital, she is encouraged to register in a hospital of her choice) for delivery, counsels on the importance of regular antenatal care, danger signs during pregnancy, on the benefits of an adequate diet during pregnancy and preparation for breastfeeding and infant care and promotes institutional delivery [43]. The workers encourage the woman for timely antenatal care (1 visit in the first trimester, 2 in the second and 5 in the third trimester). They also ensure uninterrupted supplies of iron folic acid, calcium, vitamin D and multiple micronutrient supplements to the woman throughout pregnancy [43].

Milk is delivered to pregnant women through neighbourhood depots; an attempt is made to observe the intake and compliance is documented at each visit.

Women are encouraged to consume snacks given to them (details given earlier). Monthly weight measurements are taken at home or at the outreach clinic.

The collaborating hospital follows the WHO recommendations on antenatal care [43]. The first visit for registration and the visits in the last trimester are done in Safdarjung Hospital. Women with complications (hypertension, gestational diabetes, severe anemia, previous bad obstetric history etc) are encouraged to visit the hospital for all antenatal visits; those without complications may use the outreach clinic.

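### The pre-conception comparison (A+B vs C+D) is labelled intention-to-treat, yet only about 31.5% of randomised women are expected to contribute birth outcomes, and the package could influence which women these are

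*Protocol article*

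**What the plan says.** Groups: A receives both packages, B the pre-conception package only, C the pregnancy and early-childhood package only, and D routine care.

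- Main effects: "Analysis will be done by intention-to-treat". No analysis set is defined there. Primary comparisons lists A+B vs C+D as one of the two factorial comparisons, for birth outcomes and for length at 24 months.
- Sample size: "We propose to enrol a total of 13,500 eligible women", 6750 per arm. One conception rate is applied to everyone: "45% of reproductive-age women randomized get pregnant in the 18 months of the pre- and peri-conception intervention period". For the stage after conception the plan allows "30% loss (abortions, still births, maternal deaths, moving away, refusals) between pregnancy and live birth". For the stage after delivery its allowance is "20% loss (loss-to-follow-up and child deaths) between birth and 24 months of age".
- Entry to the second phase, under the heading on the period after the second randomisation: "If women are eligible at rescreening (not moving away from the study area) and consent is given for further participation". Randomization, allocation and masking says that participants cannot be masked.
- Intervention delivery, Pre- and peri-conception period: "Family planning advice is offered to recently (< 1 year) married women, those with a young (< 1 year) child". The same sentence extends the advice to women with anaemia above the mild grade, reproductive tract or sexually transmitted infection, undernutrition, thyroid disease or diabetes under treatment.
- Table 3 lists weekly iron-folic acid as the only pre-conception component for controls.
- Comparability between the two groups: "Our large sample size is likely to yield a balance between the groups". It then undertakes to examine baseline differences and to adjust for imbalanced characteristics that may influence the primary outcomes. Flow of participants promises numbers and reasons for exclusion at all time points.

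**The concern.** The first randomisation takes place before conception, but every primary outcome is measured on a child. A+B vs C+D is therefore a comparison within a subset defined by events after randomisation: conceiving in the window, staying in the area, consenting again while knowing one's allocation, and delivering. Randomisation guarantees comparability of the 6750 and 6750 women enrolled. It does not guarantee comparability of those who reach a birth.

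Most pre-conception trials condition on birth in this way. Here one component of the package bears directly on whether and when a woman conceives, and some of its triggers are also prognostic for the outcomes. If advised women conceived less often within the window in one arm only, the mix of mothers would differ between A+B and C+D, and outcome rates could differ with no change in any pregnancy.

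This matters because the Discussion and Conclusion present the effect of pre-conception intervention as a main reason for the factorial design and as a basis for policy.

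**Working it through.** **1. The plan's own numbers.** Inputs are from Sample size.
- Pregnancies: 13,500 × 0.45 = 6075.
- Live births: 6075 × 0.70 = 4252, so 2126 per side of A+B vs C+D and 4252 / 4 = 1063 per group. The plan states about 1100, which is the same figure to the nearest hundred.
- Children at 24 months: 4252.5 × 0.80 = 3402, or about 850 per group. The plan states a floor of 600 per group.

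**2. Share of first-randomised women who contribute.**
- Birth outcomes: 0.45 × 0.70 = 31.5%, so 68.5% are outside the analysis.
- 24-month outcomes: 0.315 × 0.80 = 25.2%, so 74.8% are outside. At the plan's floor of 2400 children the share is 2400 / 13,500 = 17.8%.

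**3. Do the triggers for advice overlap with prognosis?** The Background ties undernutrition, hypothyroidism, diabetes and reproductive tract infection to birth or infant outcomes. All four are among the triggers. Recent marriage and a young child are also triggers, but the documents give no excess risk for these women.

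**4. How large could the distortion be?** The documents give no conception rate by arm and no LBW rate by risk group, so the inputs here are assumptions. Let s be the share of the arm that is advised, c the relative cut in their conceptions within the window, and g their excess LBW rate in percentage points. With no true effect:

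shift = [s − s(1−c) / (s(1−c) + 1 − s)] × g

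- s = 0.20, c = 0.10, g = 7.5: (0.2000 − 0.18/0.98) × 7.5 = 0.12 points.
- s = 0.20, c = 0.30, g = 7.5: (0.2000 − 0.14/0.94) × 7.5 = 0.38 points.
- s = 0.60, c = 0.50, g = 12.5: (0.6000 − 0.30/0.70) × 12.5 = 2.14 points.

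The planned LBW effect is 25% × 0.25 = 6.25 points, so these are 2%, 6% and 34% of it. The last case implies a 0.60 × 0.50 = 30% relative fall in conceptions across the arm.

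**5. Effect on the test.** A second assumed grid takes a high-risk share h of 20–40% (the setting's undernutrition rate of about 22% is a lower anchor), an LBW risk ratio r of 1.5–2.0 in those women, and a cut q of 10–50%. Overall LBW without selection is 25%.
- Mid case h = 0.30, r = 2.0, q = 0.25: low-risk rate 0.25 / 1.3 = 0.1923; high-risk share after selection 0.225 / 0.925 = 0.2432; LBW 0.1923 × 1.2432 = 0.2391. The relative risk is 0.956, and a two-sided 5% test rejects about 13% of the time.
- Across the grid the relative risk runs from 0.99 to 0.89 and the rejection rate from 5% to 49%. The top case (h = 0.40, r = 2.0, q = 0.50) moves LBW from 25.0% to 22.3%, or 2.7 points. It exceeds the top of step 4 because its risk gap is wider: 0.25 / 1.4 = 17.9 points.

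**6. What can be corrected from the data.** Height, weight, age, number of children and education are available in both arms. Laboratory investigations describes enrolment blood sampling for the intervention group only. Anaemia, thyroid and diabetes status at enrolment is therefore unknown in controls. Blood taken in both arms when pregnancy is reported comes after the package has acted and cannot stand in for a baseline value.

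**The case against.** The case on the other side is substantial.

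- A reader might infer that the plan relies on sample size alone. It does not: the sentences after that remark promise adjustment, and participant flow is promised with reasons at all time points. A large difference in conception between arms would probably show there.
- Intention-to-treat can be read as analysed as allocated. Birth weight cannot exist for a woman who did not conceive, and covariate lists and sensitivity analyses usually sit in an analysis plan.
- The stated principle of the package is that women be healthy when they conceive. Postponement within the 18 months removes nobody from the analysis and is part of the intended effect. Only postponement beyond the window, or effects on re-consent and loss, select.
- A reader might infer that the package lowers conception among high-risk women, so that a benefit in A+B would be an artefact. The documents do not support this. All enrolled women wish to have a child, treatment of illness could raise conception in the same women, and the advice also reaches women with no documented excess risk.
- The section on the advice does not say outright that controls receive none, and controls keep access to usual care. Its absence for them is inferred from Table 3 and from the delivery team being informed only of intervention women.

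All of this stands as a limit on direction and size. It does not restore the protection of randomisation to the analysed set. Adjustment for imbalances seen in measured characteristics is also a weaker safeguard than a pre-specified model when selection may act on characteristics not measured in one arm.

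**Conclusion.** The point holds as a matter of label, estimand and pre-specification. A+B vs C+D is not an intention-to-treat comparison over all randomised women: on the plan's assumptions 31.5% contribute at birth and 25.2% at 24 months. The package could alter which women these are. Whether it does, and in which direction, cannot be known from the documents.

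The size is illustrative. The first set of assumptions gives a spurious LBW difference of about 0.1 to 2.1 points against the planned 6.25; the second, with a wider risk gap, reaches 2.7. At the mild end the distortion is negligible.

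A reader might also infer that A+C vs B+D is wholly unaffected. It is free of selection through conception, because it is randomised afterwards. It still conditions on losses between the second randomisation and live birth; the 30% allowance covers these losses but is not split by timing.

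**What to change.** For A+B vs C+D:

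1. Pre-specify adjustment for enrolment height, BMI, age, parity (none or one child) and education, all available in both arms, whatever imbalance is seen.
2. Report conception, re-consent, fetal loss and live birth by first-randomisation arm, with all 6750 women in each arm as denominator, and tabulate enrolment characteristics of the women analysed.
3. Add a sensitivity analysis for selection, for example weighting by the inverse probability of reaching a birth given arm and enrolment covariates. State that enrolment anaemia, thyroid and diabetes status is not measured in controls, so this cannot fully remove the bias.
4. Describe the result as an effect among births to re-randomised women, analysed as allocated.

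For A+C vs B+D, state that the analysis follows allocation at the second randomisation and conditions on reaching a birth.

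The cost is wording and modest extra analysis of data already collected, with a more cautious label for the pre-conception result. No change to clinical care is proposed.

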### Randomization, allocation and masking

The randomization list was prepared by an independent statistician at World Health Organization (WHO) using random permuted blocks, stratified by maternal height [< 150 cm (< − 2 SD) and ≥ 150 cm (≥ − 2 SD)] of the WHO standards [58].

The first randomization is done at enrollment when married women aged 18 to 30 years fulfil the eligibility criteria and consent to participate in the study. The second randomization is done when women become pregnant during the 18 months follow up period, and are eligible (not moving away from the study area) at rescreening and consent to their own and their baby’s participation in the study. The group allocation is done through a web-based system. There are no additional criteria for discontinuation or modification of allocated interventions.

Masking participants and study teams is not possible because of the nature of interventions in this trial. However, attempts are made to keep the independent outcome ascertainment team unaware of the group allocation, to the extent possible.

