### Statistical analyses

#### Primary comparisons

The primary analysis will be factorial, for comparison of the pre- and peri-conception intervention package (pre- and peri-conception intervention package alone or with enhanced antenatal, postnatal and early childhood care package i.e. Group A + B) with no pre- and peri-conception intervention package (enhanced antenatal, postnatal and early childhood care package alone or routine care i.e. Group C + D), and the enhanced antenatal, postnatal and early childhood care (with pre- and peri-conception intervention package or enhanced antenatal, postnatal and early childhood care alone i.e. Group A + C) with no enhanced antenatal, postnatal and early childhood care (pre- and peri-conception intervention package alone or routine care i.e. Group B + D) on birth outcomes (mean birth weight and length, proportion stunted at birth, proportion of babies born preterm and spontaneous preterm births, SGA and LBW) and mean length for age z-score and proportion stunted at 24 months.

In addition to the factorial analysis, we will also examine the impact of the combined pre- and peri-conception intervention package and enhanced antenatal, postnatal and early childhood care (Group A) on birth outcomes and attained length at 24 months of age, compared to routine care (Group D).

We will examine if there is an interaction between the intervention package delivered during peri-preconception period and that delivered during antenatal and early childhood period on primary outcomes.

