#### Pre-specified subgroup analysis

We will conduct subgroup analysis for women according to their height (< 150 cm and ≥ 150 cm), underweight, BMI status at enrolment and at the time of pregnancy confirmation, years of education and high risk pregnancy. We will also conduct subgroup analysis by wealth quintile of the household. The relative measures of effect within each of these subgroups will be estimated.

The effect of interventions on secondary outcomes will be assessed using the same models as for primary outcomes.

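### Covariates for the primary outcomes are to be picked from observed baseline imbalance, with no list or threshold, and the primary model text does not name the maternal-height stratum

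*Protocol article*

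**What the plan says.** Randomization, allocation and masking: the list was prepared "using random permuted blocks, stratified by maternal height", with the cut at 150 cm. The Background links short maternal height to undernutrition in the offspring. Screening and enrollment has height and weight measured before the woman is allocated.

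Comparability between the two groups: no significance tests will be done on baseline characteristics. Instead, "we will carefully examine the size of any baseline differences", and then "Imbalanced characteristics that may influence the primary outcomes will be adjusted appropriately".

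Main effects gives the models. "For binary outcomes, generalized linear models (GLMs) of the binomial family with a log-link function will be used to calculate the effect size", and "For continuous outcomes, GLMs of the Gaussian family with an identity-link function will be used to calculate the effect size". It specifies family, link and effect measure. It names no covariate, and it does not say that the models are unadjusted.

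Primary comparisons: "The primary analysis will be factorial, for comparison of the pre- and peri-conception intervention package", and likewise for the pregnancy and early-childhood package. It adds: "We will examine if there is an interaction between the intervention package delivered during peri-preconception period" and the later package.

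**The concern.** The imbalance rule is stated outright, so it is not merely a detail left to a fuller document. It has two weaknesses. First, the adjusted model cannot be known until baseline data by arm have been inspected, and no criterion says how large a difference counts or which characteristics qualify. Two analysts following the sentence faithfully could report different primary estimates. The three comparisons (A+B vs C+D, A+C vs B+D, A vs D) could also end with different covariate sets. Second, imbalance is a poor reason to choose a covariate. A strong predictor improves precision even when it is balanced, and the rule would pass it over.

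Maternal height is the clearest case. Stratified allocation tends to balance it, so an imbalance rule is unlikely to select it. Yet the design uses it as the stratification factor and the Background treats it as prognostic. An analysis that ignores a prognostic stratification factor gives standard errors slightly too large for the design.

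**Working it through.** **Reproducing the plan's figure.** Table 1 gives 935 per pooled side for mean LAZ (0.15 SD, 90% power, 95% confidence). An unadjusted two-group comparison needs n = 2(1.960 + 1.282)²/0.15² = 934, so the figure reproduces. Power at 935 by the same formula is 90.0%.

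**Leaving out the stratum, continuous outcome.** The article gives neither the share *s* of women below 150 cm nor the LAZ difference *d* (in SD) between strata. Assumed: *s* = 10-50%, *d* = 0.2-0.6. The stratum explains R² = s(1−s)d² of the variance. If balance within strata holds among the children analysed:
- true alpha without the stratum = 2Φ(−1.96/√(1−R²))
- power without it = Φ[(0.15/√(2/935) − 1.96)/√(1−R²)]
- power with it = Φ[0.15/√(2(1−R²)/935) − 1.96]
- n with it = 935(1−R²)

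| s | d | R² | alpha without | power without | power with | n with |
|---|---|---|---|---|---|---|
| 0.1 | 0.2 | 0.0036 | 0.0496 | 90.1% | 90.1% | 932 |
| 0.3 | 0.4 | 0.0336 | 0.0462 | 90.4% | 91.0% | 904 |
| 0.5 | 0.6 | 0.0900 | 0.0399 | 91.1% | 92.5% | 851 |

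The alpha column shows the most conservatism to expect. By the Sample size assumptions only 0.45 × 0.70 = 31.5% of women first randomised reach a live birth and 0.315 × 0.80 = 25.2% reach 24 months, so balance set at enrolment carries over only in part. With no carry-over, alpha without the stratum returns to 0.05 and power to the planning value of 90.0%. The with-stratum figures are unaffected.

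**Leaving out the stratum, stunting.** The overall rate is 30% (Table 1). Assumed risk ratio, short to tall mothers: 1.5-2.0. The tall-stratum rate is 0.30/(1−s+s·RR), and R² = s(1−s)(difference in rates)²/(0.30 × 0.70). At s = 0.3 and RR = 2.0 the rates are 0.231 and 0.462, R² = 0.0533 and alpha = 0.044. Over the assumed range alpha is 0.044-0.049.

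**Leaving out the other randomised factor.** With 1:1 allocation R² = 0.25d². For d = 0.15-0.20, R² is 0.0056-0.0100, alpha is 0.049, and n moves from 935 to 930-926. This is negligible.

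**The imbalance rule.** Assumed: 10 independent prognostic covariates with joint R² 0.10, 935 per side. A standardised difference has standard error √(2/935) = 0.046 under randomisation. One covariate exceeds 0.05 with probability about 0.28, so at least one of ten does so with probability 1 − 0.72¹⁰ ≈ 0.96. For a cut at 0.10 the corresponding figures are about 0.031 and 0.27. A simulation of 400,000 trials under the null gave:

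| threshold | any covariate selected | alpha, rule followed | alpha, better of adjusted and unadjusted |
|---|---|---|---|
| 0.05 | 96% | 0.044 | 0.059 |
| 0.10 | 27% | 0.048 | 0.053 |

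The same simulation gave 0.050 both for the unadjusted analysis and for all ten covariates fixed in advance.

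**Precision from height plus BMI.** No correlation is given. For assumed r = 0.2-0.35 with a continuous outcome, residual variance is 1−r² = 0.96-0.88 and the equivalent sample gain is 1/(1−r²) − 1 = 4-14%. It is less for binary outcomes.

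**The case against.** A reader might infer that the primary models omit the height stratum and the other randomised factor, and are plain unadjusted comparisons. The article does not support that. Main effects is silent on covariates, and a condensed article may leave the list to the full protocol or the SAP. For the other factor the inference is weaker still: the analysis is called factorial, and the planned interaction analysis needs both factors in a model. Nor does the article say that imbalanced characteristics are the only ones to be adjusted for.

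A reader might also take 4-14% as the cost of the present plan, or suppose that the estimates are biased. The percentage rests on assumed correlations for height plus BMI, not on the binary stratum. With balanced allocation, leaving the stratum out biases neither the difference in means nor the marginal relative risk.

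It is fair to add that the plan has margin where precision would gain most. It expects at least 600 children per group at 24 months, so 1200 per side against 935 for LAZ, and about 2200 births per side against 935 for birth weight. Preterm birth is tight (2193 needed), but it is binary. Height also has its own subgroup analysis. Followed as written, the rule does not inflate alpha; inflation needs selective reporting, which the article does not propose.

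All of this limits the size of the point. It does not answer the rule itself: a list fixed in advance elsewhere would replace the stated sentence, not complete it.

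**Conclusion.** The point stands in modest form, and its firm part is the imbalance rule. As written, the covariates behind the primary estimate are settled only after baseline differences are seen. Under the simulated assumptions, a threshold of 0.05 or 0.10 decides whether adjustment happens in 96% or 27% of trials.

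The stratum is the lesser part and is conditional on its being left out. The consequence would then be slightly wide intervals. Under the assumed strata, alpha is about 0.040-0.0496 where balance carries through to the children analysed. Power is 90.0% by the planning formula (at most 91.1% with full carry-over), against 90.1-92.5% with the stratum. No stated sample size depends on this.

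**What to change.** In Comparability between the two groups, replace the imbalance rule with a covariate set fixed before data by arm are seen. In Main effects, state that every primary model includes the maternal-height stratum (or continuous enrolment height) and enrolment BMI. For clarity, also state that both randomised factors are included. Keep the unadjusted model, and any model adjusted for observed imbalance, as sensitivity analyses. If the SAP already holds such a list, the article's rule should be marked as superseded.

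The cost is wording, since height and weight are already measured before allocation. The one technical risk is that a log-binomial model with a continuous covariate may fail to converge. Name the fallback in advance, for example modified Poisson regression with robust variance.
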